The primary outcome measure is the frequency of advanced-stage cancers detected during the course of the 2 ½ year study. These advanced-stage cancers may be detected during the study's planned screenings, through progression of preclinical disease to clinical symptomatic disease, and, less frequently, during medical testing/screening for other purposes (e.g. presurgical work-up). Advanced-stage cancers will be defined as stage III or IV cancers and will be assessed as clinically indicated, which usually includes PET imaging, additional invasive testing (i.e. tissue sampling), and sometimes brain imaging.

12.2 **SECONDARY ENDPOINT ASSESSMENT**

A secondary endpoint is the presence/absence of symptomatic lung cancer. To assess this outcome, an expert outcome review committee, consisting of a pulmonologist and an oncologist, will be convened at the end of the study (after March 2011). The committee members, each working independently, will review all cases of diagnosed, pathology-proven lung cancer as well as all deaths. Committee members will be blinded to the randomization assignment of the subjects and results of screening tests. Based on the subject’s self-reported symptoms assessment during the study and their medical records, and death certificates (if appropriate and available) the committee members will determine whether the subject is asymptomatic or has symptoms that correlate with their diagnosis of lung cancer. Subjects determined to have symptoms of lung cancer by both committee members will be classified as events for calculation of this secondary endpoint. In cases where the two committee members disagree, the committee members will meet to discuss the cases and reach consensus. Deaths due to lung cancer and deaths due to the management or treatment of diagnosed lung cancer will also be classified as events. For all events, committee members will decide on, to within 6 months, the time at which the subject developed symptoms.

Note that for the assessment of the primary and secondary endpoints, subjects who are determined to have lung cancer that has metastasized will be considered a censored event at the time of diagnosis. These subjects’ lung cancer will not be classified as events in the assessment of the primary and secondary endpoints.

Definition of "Advanced Symptomatic Disease":

The following criteria will be assessed by the Outcomes Review. All three criteria must hold.

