1. The patient has been diagnosed with non-small cell carcinoma, stage II or

higher, or small cell carcinoma, any stage.

2. The patient has experienced a symptom that led them to seek contact with a

physician since the time of the last study visit; or at the time of their next study

visit, the patient has developed a new symptom or a change in a chronic

symptom within the past 6 weeks, that did not yet lead to a doctor's visit.

3. The symptom(s) described in #2 are felt to be related to the diagnosis of lung

cancer as adjudicated by the Outcomes Review Committee.

For the other secondary endpoints, the committee will review the medical records and self-reported symptoms assessment of all deaths and determine if the death is due to lung cancer.

13.0 **STATISTICAL ANALYSIS PLAN**

13.1 **PRIMARY AIMS:**

Analyses will be based on an intent-to-treat perspective. We will test the null hypothesis that at the time of diagnosis the frequency of advanced-stage cancers is the same for screened and unscreened groups; the alternative hypothesis is that the frequency of advanced-stage cancers is different for screened and unscreened groups. These hypotheses will be tested at the end of the two and a half-year study, i.e. after March 31, 2011. The frequency of advanced-stage cancers in the two study arms will be compared using logistic regression analysis. A model will be fit to describe the probability of advanced-stage cancer as a function of the following independent variables: age, gender, symptoms status at the time of enrollment into the study (i.e. symptoms present or not present), study arm, and two-way interactions with study arm. The fit of the model will be assessed using the Hosmer-Lemeshaw goodness of fit test. The coefficients for study arm and interactions with study arm will be assessed, after adjusting for other covariates, using a likelihood ratio test with significance level of 0.05 (two-tailed).

13.2 **SECONDARY AIMS:**

One of the secondary aims of the study is to determine whether lung cancer screening using chest x-rays and CAD reduces the incidence of symptomatic advanced lung cancer relative to no screening. The observed cumulative incidence of symptomatic advanced lung cancer, measured in events per person per years observed, will be compared between the two study arms. The analysis will be carried out from an intent-to-treat perspective.

The incidence rate of symptomatic lung cancer will be estimated as follows

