The following assumptions were made for determining the required sample size for the primary study aim: prevalence of cancer at baseline screen=1%; annual incidence of cancer=0.5%; annual lost to follow-up=10%; 90% of people randomized to screening are compliant at each screening; 12-month recruitment period; 1 incident screen planned for 12 months after the initial prevalence screen; and 85% sensitivity of chest x-ray with CAD. For development of symptoms following the development of preclinical disease, we assume a uniform distribution over 30 months so that the average time is 16 months from development of detectable preclinical disease until development of symptoms. We assume a 70% reduction in the development of advanced-stage cancers if preclinical disease is detected at screening.

*Placebo Arm:*

Based on these assumptions, if N patients are randomized to the placebo arm, then after one year the number of symptomatic, advanced-stage cancers will be:

(1-lost-to-follow-up rate)(prevalence) (rate of development of symptoms over 12 months)(N).

Similarly, at year two the number of symptomatic, advanced-stage cancers will be approximately:

(1-lost-to-follow-up rate)2 (prevalence) (rate of development of symptoms over 24 months)(N)

for those with preclinical disease at the time of enrollment.

In addition, there are

(1-lost-to-follow-up rate)(incidence)(rate of development of symptoms over 12 months)(N’)

symptomatic, advanced-stage cancers from those who develop lung cancer within the first year, where N’=N-(N)(prevalence).

*Screened Arm:*

If N patients are randomized to the screening arm, and if we assume that at the time of baseline screening, 30% of detected preclinical disease is advanced-stage cancer, then the number of detected advanced-stage cancers detected at baseline is M, where

M = (prevalence)(sensitivity) (0.30)(N).

After one year the number of advanced-stage cancers will be approximately:

(1-lost-to-follow-up rate) (prevalence)(sensitivity)(rate of development of symptoms over 12 months) (N-M)(1-risk reduction due to early treatment) for those cancers detected at baseline but still progressed to symptomatic, advanced-stage cancers in one year.

In addition, there are those cancers undetected at baseline that progress to symptomatic, advanced-stage cancers in the first year:

(1-lost-to-follow-up rate)(prevalence)(1-sensitivity) (rate of development of symptoms over 12 months)(N-M).

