We estimate that if the frequency of advanced-stage cancers at two years is 1.19% for controls and 0.77% for the screened arm (difference of 0.42%), then we can detect this difference with 4000 subjects per study arm with 77% power (5% type I error rate, two-tailed test).

15.0 **COST-EFFECTIVENESS ANALYSIS**

The cost effectiveness analysis will be performed only on subjects who declare themselves as Cleveland Clinic patients at entry into the study. The rationale is based on experiences from other studies where it was found to be impossible to collect valid medical visit and hospital stay data from other medical institutions even when the study subject had signed a medical release form. Thus, it was decided that the cost-effectiveness assessment in this study would be limited to Cleveland Clinic patients for whom medical records could more easily and reliably be obtained. We recognize that this decision limits the generalize ability of our cost effectiveness analysis results.

This analysis will be conducted from the US societal perspective as recommended by the U.S. panel for cost effectiveness in health and medicine.24 The initial time horizon will be the three-year study period, but will also be extended to 10 and 20 years using Markov modeling approach to measure the long-term cost-effectiveness difference between lung cancer screening and placebo screening. When data are collected after each visit, the intermediate analysis will be conducted to analyze the short-term cost-effectiveness outcomes if necessary. The results from the intermediate study could be used to guide the concurrent treatment in clinical settings.

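### Section 14 implicitly counts every symptomatic lung cancer as stage III/IV; for any smaller share, the planned 0.42% difference is overstated

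*Protocol*

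**What the plan says.** Section 12.1 defines the primary endpoint by stage: "Advanced-stage cancers will be defined as stage III or IV cancers". It counts such cancers whether found at a study screen, through symptoms or, less often, during testing for other reasons. Section 13.1 refers the comparison to stage at the time of diagnosis.

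Section 14.0 lists its planning assumptions for the primary aim and then builds expected counts. For placebo it writes "if N patients are randomized to the placebo arm, then after one year the number of symptomatic, advanced-stage cancers will be", followed by a product whose first-year form is ("1-lost-to-follow-up rate)(prevalence) (rate of development of symptoms over 12 months)(N"). The 24-month term for prevalent cancers and the term for first-year incident cancers have the same structure. None contains a stage fraction.

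For the screened arm, Section 14 does use a stage fraction where the cancer is found at a screen. At baseline it assumes that "30% of detected preclinical disease is advanced-stage cancer", and at the one-year screen it uses 15%. Its terms for cancers that reach the endpoint through symptoms again carry no stage fraction.

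Table 2 gives 47.5 placebo and 30.9 screened events at 4,000 per arm. The rates carried into the power statement are "1.19% for controls and 0.77% for the screened arm (difference of 0.42" per cent).

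**The concern.** If some cancers that come to light through symptoms are not yet stage III or IV, the symptom-route terms count cancers that the endpoint excludes. The assumption that none are is neither listed with the other inputs nor justified, and it fits poorly with the rest of the protocol. Section 2.0 says only that a large share of people with lung cancer present late. The definition of advanced symptomatic disease in section 12.2 makes stage a criterion separate from symptoms and admits lower stages: "The patient has been diagnosed with non-small cell carcinoma, stage II or" higher, or small cell carcinoma of any stage.

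The omission does not cancel between arms. The whole placebo count comes through the symptom route, whereas part of the screened-arm count comes from screen detection and already carries a stage fraction. The design difference and the expected event total, on which the sample size rests, therefore both depend on an unstated number.

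**Working it through.** **Inputs (section 14.0).** Prevalence 1%; annual incidence 0.5%; annual loss 10% (retention 0.90, and 0.81 over two years); compliance 90%; sensitivity 85%; risk reduction after detection 70% (residual 0.30); stage fractions 30% and 15% for screen-detected cancers. Symptom onset is uniform over 30 months, so the rates are 12/30 = 0.40 and 24/30 = 0.80. N = 4,000 per arm and N′ = 4,000 − 40 = 3,960.

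**Step 1: reproduce Table 2.**

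Placebo:
- year 1, prevalent: 0.90 × 0.01 × 0.40 × 4000 = 14.40
- 24 months, prevalent: 0.81 × 0.01 × 0.80 × 4000 = 25.92
- incident: 0.90 × 0.005 × 0.40 × 3960 = 7.13
- sum: 47.45 (Table 2: 47.5)

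Screened arm, found at a screen (stage fraction applied):
- M = 0.01 × 0.85 × 0.30 × 4000 = 10.20
- M′ = 0.90 × 0.90 × 0.005 × 0.85 × 0.15 × 3960 = 2.04
- sum: 12.24

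Screened arm, symptom route (no stage fraction), with N − M = 3989.80 and N′ − M′ = 3957.96:
- year 1, detected: 0.90 × 0.01 × 0.85 × 0.40 × 3989.80 × 0.30 = 3.66
- year 1, missed: 0.90 × 0.01 × 0.15 × 0.40 × 3989.80 = 2.15
- 24 months, detected: 0.81 × 0.01 × 0.85 × 0.80 × 3989.80 × 0.30 = 6.59
- 24 months, missed: 0.81 × 0.01 × 0.15 × 0.80 × 3989.80 = 3.88
- incident, detected: 0.81 × 0.90 × 0.005 × 0.85 × 0.40 × 3957.96 × 0.30 = 1.47
- incident, missed: 0.81 × 0.005 × 0.15 × 0.40 × 3957.96 = 0.96
- sum: 18.72

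The screened total is 12.24 + 18.72 = 30.97 before rounding (Table 2: 30.9). The rates are 47.45/4000 = 1.186% and 30.97/4000 = 0.774%, a difference of 0.412% against the stated 0.42%. The match leaves no room for a hidden stage factor.

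**Step 2: insert the missing factor.** Let f be the share of symptomatic cancers that are stage III/IV, taken as equal in both arms. The documents give no value, so the range below is an assumption.

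- placebo = 47.45f
- screened = 12.24 + 18.72f
- difference = (28.73f − 12.24)/4000
- total events = 12.24 + 66.17f

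| f | placebo | screened | total | difference |
|---|---|---|---|---|
| 1.0 | 47.4 | 31.0 | 78.4 | 0.41% |
| 0.9 | 42.7 | 29.1 | 71.8 | 0.34% |
| 0.8 | 38.0 | 27.2 | 65.2 | 0.27% |
| 0.7 | 33.2 | 25.3 | 58.6 | 0.20% |

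The total reaches 70 at f = (70 − 12.24)/66.17 ≈ 0.87.

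**Step 3: does the direction depend on modelling choices?** Suppose f is applied only to placebo cancers and to cancers missed at screening, leaving the detected-but-progressing terms unscaled. The difference is then smaller still: 0.31%, 0.21% and 0.11% at f = 0.9, 0.8 and 0.7. Scaling every symptom term is the milder correction.

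**The case against.** The strongest defence is that Section 14 labels these terms both symptomatic and advanced-stage, so onset of symptoms may be a deliberate stand-in for progression to advanced stage. On that reading f = 1 is a planning simplification, and the formulas do deliver about 0.41% under it. That stands as far as it goes. It does not explain why an input of this weight is missing from the list of assumptions, or why stage is modelled for one route of detection and not the other.

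Several stronger readings are tempting, but the documents do not support them.
- **That the protocol refutes f = 1 with a figure.** It does not. Section 2.0 speaks of lung cancer patients in general, and the section 12.2 definition belongs to a secondary endpoint. They point to a share below 1 without setting one.
- **That Table 2 counts symptomatic cancer instead of the primary endpoint.** It mixes routes: 12.24 of the 30.97 screened events are advanced cancers found at a screen, as section 12.1 allows.
- **That 0.42% does not follow from the plan's own assumptions.** It does, once f = 1 is admitted as one of them.

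Two further limits stand. Section 14 also has no term for advanced cancers found incidentally. Adding them to placebo would act in the opposite direction, although section 12.1 calls that route less frequent.

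The same figures also carry separate errors. The 24-month prevalent term already includes the first 12 months, yet both are added. Without the year-1 terms the counts are 47.45 − 14.40 = 33.05 and 30.97 − 5.82 = 25.15, a difference of 7.90/4000 = 0.20% and a total of about 58, already under 70 at f = 1. The stated 77% power does not reproduce either; the stated rates give about 48% at 4,000 per arm. The 0.87 crossing point therefore holds only within Table 2's own summation.

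**Conclusion.** The point holds as an unstated and unjustified assumption that favours the design. For any f below 1, with the other inputs and Table 2's summation held and f equal in both arms, the planned difference is overstated. About a sixth of it goes at f = 0.9 (0.41% to 0.34%) and about a third at f = 0.8 (to 0.27%). The direction is certain under those conditions. The size is a range only, because the documents give no f.

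This should be fixed, but it does not undermine the trial. The power statement is conditional on the stated rates, and the endpoint, hypothesis and planned test do not change. A reader might infer that a null result would be uninterpretable. The documents do not support that, since the result will be read from the observed data.

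**What to change.** In section 14.0:
- State f, the assumed share of symptomatic lung cancers that are stage III/IV at diagnosis, with its source.
- Multiply every symptom-route term in both arms by f, and keep the 30% and 15% for screen-detected cancers.
- Say that advanced cancers found incidentally are not modelled.
- Restate Table 2, the 1.19% and 0.77% rates, the difference and the comparison with the 70-event minimum, with a short sensitivity table over f.
- Make these changes together with the corrections to the summation and the power statement, so that the figures are restated once.

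The cost is a recalculation and a few sentences. The downside is a less favourable stated difference and event count. Enrolment and conduct need no change on this account.

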At the one-year incident screen we assume that 15% of detected preclinical disease is advanced-stage cancers. Thus, at the incident screen, M’ advanced-stage cancers will be detected:

M’= (1-lost-to-follow-up rate)(compliance rate with screening)(incidence rate)(sensitivity) (0.15)(N’).

At year two, the number of symptomatic, advanced-stage cancers will be approximately:

(1-lost-to-follow-up rate)2 (prevalence)(sensitivity) (rate of development of symptoms over 24 months)(N-M)(1-risk reduction due to early treatment) for those with preclinical disease detected at the time of enrollment but still progressed to advanced-stage cancers by two years.

In addition, there are those cancers undetected at baseline that progress to symptomatic, advanced-stage cancers over 24 months: (1-lost-to-follow-up rate)2 (prevalence)(1-sensitivity) (rate of development of symptoms over 24 months)(N-M).

There are also cancers that developed over the first year, were detected at the incident screen, and became symptomatic, advanced-stage cancers during the second year:

(1-lost-to-follow-up rate)2 (compliance rate with screening)(incidence)(sensitivity)(rate of development of symptoms over 12 months)(N’-M’)(1-risk reduction due to early treatment).

Finally, there are cancers that developed over the first year, were undetected at the incident screen, and became symptomatic, advanced-stage cancers during the second year:

(1-lost-to-follow-up rate)2 (incidence)(1-sensitivity)(rate of development of symptoms over 12 months)(N’-M’).

Table 2 summarizes the number of advanced-stage lung cancers expected in the two study arms as a function of N.

| N, # subjects per study arm | # advanced-stage cancers in placebo arm | # advanced-stage cancers in screening arm | Total Number of advanced-stage cancers |
| --- | --- | --- | --- |
| 3000 | 35.6 | 23.2 | 58.8 |
| 3500 | 41.6 | 27.1 | 68.7 |
| 4000 | 47.5 | 30.9 | 78.4 |
| 4500 | 53.4 | 34.7 | 88.1 |
| 5000 | 59.3 | 38.7 | 98.0 |

We plan to fit a logistic regression model to describe the probability of advanced-stage lung cancer as a function of 1) patient age, 2) gender, 3) symptoms status at time of enrollment, and 4) study arm randomized to. We will also consider in the model all two-way interactions with study arm. The rule of thumb to avoid model overfitting is at least 10 events per independent variable in the model, thus we need at least 70 advanced-stage cancers (total) for the model building.

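### Section 14 subtracts already-advanced screen-detected cancers from subjects instead of from detected cancers, so about 3.3 screened-arm events are counted twice at 4000 per arm

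*Protocol*

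**What the plan says.** Section 14 builds the expected number of advanced-stage cancers in each arm from stated assumptions, among them "prevalence of cancer at baseline screen=1" per cent, "annual incidence of cancer=0.5" per cent, "annual lost to follow-up=10" per cent and "90% of people randomized to screening are compliant at each screening". For the screened arm it assumes that "30% of detected preclinical disease is advanced-stage cancer" at the baseline screen, and sets M equal to prevalence × sensitivity × 0.30 × N. At the incident screen the advanced share is 15%, which gives M'.

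The year-one progression term for baseline-detected cancers multiplies prevalence, sensitivity, the symptom rate and the retention rate by "N-M)(1-risk reduction due to early treatment) for those cancers detected at baseline but still progressed". The year-two term has the same structure: "N-M)(1-risk reduction due to early treatment) for those with preclinical disease detected at the time of enrollment". The terms for undetected cancers also use N−M, and both incident-cancer terms use N'−M'.

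Table 2 gives 47.5 placebo and 30.9 screened events at 4000 per arm, 78.4 in total. The power statement uses "1.19% for controls and 0.77% for the screened arm (difference of 0.42" points and reports 77%. The same section asks for at least 70 advanced-stage cancers to support the logistic model.

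**The concern.** M is a count of cancers and N is a count of people. Taking 10.2 from 4000 people and then multiplying by prevalence × sensitivity (0.0085) removes only 0.09 of a cancer from a detected pool of 34, when the evident purpose is to remove 10.2. The already-advanced cancers enter the total once through M and stay in the pool from which further advanced cancers are drawn.

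The primary outcome in Sections 12.1 and 13.1 is whether a subject has a stage III or IV cancer, analysed as one binary outcome per subject. A cancer advanced at detection cannot supply a second event, and a treatment benefit defined as preventing advanced disease cannot apply to it.

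At stake are the screened-arm rate, the planned difference and the event total that is held against the 70-event minimum. Only the screened arm is affected.

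**Working it through.** **Inputs (all Section 14).** Prevalence p = 0.01; incidence i = 0.005; retention 0.9 per year; compliance c = 0.9; sensitivity s = 0.85; risk reduction 0.70, so a factor 0.3 remains; advanced shares 0.30 and 0.15. Symptom onset is uniform over 30 months, read as 12/30 = 0.40 and 24/30 = 0.80. N = 4000 and N' = 4000 − 40 = 3960.

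**Step 1: reproduce Table 2.**

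M = 0.01 × 0.85 × 0.30 × 4000 = 10.20. M' = 0.9 × 0.9 × 0.005 × 0.85 × 0.15 × 3960 = 2.04. So N−M = 3989.8 and N'−M' = 3957.96.

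| Screened-arm term | As printed | M, M' taken from cancers |
|---|---|---|
| M | 10.20 | 10.20 |
| Detected at baseline, year 1 | 3.66 | 2.57 |
| Undetected at baseline, year 1 | 2.15 | 2.16 |
| M' | 2.04 | 2.04 |
| Detected at baseline, year 2 | 6.59 | 4.63 |
| Undetected at baseline, year 2 | 3.88 | 3.89 |
| Incident, detected | 1.47 | 1.25 |
| Incident, undetected | 0.96 | 0.96 |
| **Total** | **30.97** | **27.70** |

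Placebo: 14.40 + 25.92 + 7.13 = 47.45. Both totals match Table 2 (30.9 and 47.5). The other screened rows come out at 23.2, 27.1, 34.8 and 38.7, against 23.2, 27.1, 34.7 and 38.7 printed. Without M and M' the screened sum would be only 30.97 − 10.20 − 2.04 = 18.7, so the table does count them as events.

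**Step 2: isolate the slip.**

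- Baseline-detected pool as printed: 0.0085 × 3989.8 = 33.9. Intended: 34 − 10.2 = 23.8.
- Progression from that pool, both years: pool × 0.3 × (0.9 × 0.40 + 0.81 × 0.80) = pool × 0.3 × 1.008. As printed 33.91 × 0.3024 = 10.25; corrected 23.8 × 0.3024 = 7.20. Excess 3.06.
- Incident-detected: 0.81 × 0.9 × 0.005 × 0.85 × 0.40 × 0.3 × 3957.96 = 1.47. With 3960 × 0.85 in the last place it is 1.25. Excess 0.22.
- Undetected terms with N and N': up by 0.02 in total.
- Net change: 3.06 + 0.22 − 0.02 = 3.26 events, about 11% of 30.97.

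**Step 3: effect on the planning figures, this slip alone.**

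Power = Φ(difference/SE − 1.96), with SE = √{[p₁(1−p₁) + p₂(1−p₂)]/4000}.

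| | Screened rate | Difference | Total events | Power |
|---|---|---|---|---|
| Formulas as printed (unrounded) | 0.774% | 0.412 points | 78.4 | Φ(1.871 − 1.96) = 46% |
| Slip corrected | 0.693% | 0.494 points | 75.2 | Φ(2.289 − 1.96) = 63% |
| Printed rounded rates, 1.19% v 0.77% | 0.77% | 0.42 points | – | Φ(1.907 − 1.96) = 48% |

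**Step 4: what remains once the years are not double-summed.** Section 14 separately adds a 12-month count to a cumulative 24-month count in both arms. Using year-by-year increments (0.40 in each year), placebo is 14.40 + 12.96 + 7.13 = 34.5. Screened is 25.7 with the slip and 23.4 without it, a change of 2.3 events. The total falls from 60.2 to 57.9, and power goes from 20% to 31%. Another way to remove the double sum, keeping only the 24-month term, gives 33.0 v 25.2 with the slip and 33.0 v 23.0 without it, with power 18% and 27%.

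**The case against.** The best defence is that the slip is small and, for power, conservative. It moves the screened rate by 0.08 points, makes screening look less effective than the plan's own assumptions imply, and leaves the total at 75.2, above 70. The protocol also labels several of these counts as approximate. The direction and the size stand. The label does not excuse the slip: it has the same sign in every row of Table 2, and including N−M at all shows that the already-advanced cancers were meant to be removed. For the event total the slip is not conservative.

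Four stronger readings are tempting, and the document supports none of them.

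- *All 10.2 already-advanced cancers are counted twice.* Nearly all stay in the progression pool, but only the fraction the model lets progress is counted again: 10.2 × 0.3 × 1.008 = 3.1, plus 0.2 from the incident term.
- *0.69% is the right screened rate.* It holds every other Section 14 term fixed, and some of those err the other way. With this slip corrected, 90% compliance applied at baseline, non-compliers treated as undetected at the incident screen, and two years' loss applied to the placebo incident term, the counts are 46.7 v 29.9 (0.75%, power 49%). With 100% baseline compliance they are 46.7 v 28.2 (57%).
- *The slip explains the 77% power.* It does not. The printed rates give 48% at 4000 per arm; about 8000 per arm would be needed for 77%. That is a separate defect.
- *The slip takes the trial below 70 events.* Alone it does not. The total falls below 70 only when the double-summed years are corrected, and it does so then with or without this slip (57.9 or 60.2).

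**Conclusion.** The point holds as an algebraic error in the screened-arm formulas. At 4000 per arm it double-counts about 3.3 events (3.1 baseline, 0.2 incident), or about 2.3 once the years are no longer double-summed by year-by-year increments. Taken alone it overstates the screened rate by 0.08 points and the event total by 3.3, and understates the planned difference by the same 0.08 points.

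This rests on Section 14's own assumptions and on reading the uniform 30-month distribution as 0.40 at 12 months and 0.80 at 24 months, a reading confirmed by the match to Table 2. The error touches planning figures only; it does not affect the validity of the primary analysis. It deserves correction because a stated design rate does not follow from the stated assumptions, but it is not the main weakness of Section 14.

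**What to change.** - In both progression terms for baseline-detected cancers, replace (prevalence)(sensitivity)(N−M) by (prevalence)(sensitivity)(N)(1−0.30).
- In the progression term for cancers detected at the incident screen, replace (N'−M') by (N')(1−0.15).
- In the terms for undetected cancers, use N and N' with nothing subtracted, since M and M' are detected cancers.

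Do not reprint after this change alone: that would show 0.69% and 63% power, more favourable than the fuller correction supports. Make it together with the other Section 14 corrections (double-summed years, compliance, loss to follow-up and the power calculation). Then reprint Table 2, the screened rate, the difference, the event total against the 70-event minimum, and the power once from the fully corrected model.

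The cost is recalculation and protocol wording; no trial procedure changes. The expected event total becomes somewhat less favourable against the 70-event minimum.
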